## Discussion

The various projects in the EXPLICIT programme will have a major impact on treatment policies for stroke victims, acknowledging in particular that about 80% of all stroke survivors show upper limb paresis immediate after stroke [3], whereas only one third of all stroke patients have regained some dexterity at 6 months. A poor outcome of the upper limb is considered a major threat to perceived quality of life in patients suffering from stroke [4]. EXPLICIT intends to assess not only the effectiveness of early Modified CIMT and EMG-NMS for regaining dexterity, but also to examine the observed time-dependent dynamics in cortical plasticity (i.e. learning-dependent neural plasticity) and its effects on motor control. For example, EXPLICIT intends to answer the question whether therapy-induced improvements are due to a reduction of basic motor impairment by true repair (i.e. restitution of function) or to patients learning to apply compensatory movement strategies (i.e., substitution of function). This issue is perceived as a key question in the attempts to improve rehabilitation services for patients with an upper limb deficit after stroke in the near future. The 'EXPLICIT' programme is based on the hypothesis that therapy-induced cortical changes are best facilitated within the first days and weeks after stroke onset. [10,14,55,56]. EXPLICIT intends to reveal the effectiveness of early activation programmes after stroke by 1) forcing patients with a favourable prognosis to use their upper limb in a functional manner or 2) electrical stimulation of the distal paretic hand muscles in patients with an initially unfavourable prognosis for upper limb function [5]. Since 2006, meta-analyses have shown that constraining the non-paretic arm (Modified CIMT) in order to force the paretic arm into active involvement, combined with a functional exercise programme facilitating functional use, is an effective way to improve upper limb function in chronic stroke patients [17]. However, high quality RCTs started in the acute or subacute phase post stroke are lacking in the literature [6]. This makes the EXPLICIT programme innovative and unique in the field of stroke rehabilitation science. The EXPLICIT programme is based upon two hypotheses: 1) Patients with a favourable prognosis after stroke will benefit more from early Modified CIMT in terms of regaining upper limb function than from a conventional exercise programme; 2) in patients with an initial low probability of achieving some dexterity at 6 months [5], an early sensorimotor stimulation programme by means of EMG-triggered neuromuscular stimulation (EMG-NMS) of wrist and hand extensors may increase the likelihood of return of dexterity compared to an equally intensive conventional training programme. To date, the literature offers no controlled studies targeting this subgroup of patients with an unfavourable prognosis, whereas about 62% of all patients show a poor outcome of the upper limb function after 6 months [5,6] (Relevance of project A2 of EXPLICIT.)

Both projects (i.e., A1 and A2) are particularly relevant since the functional outcome of the paretic upper limb is largely defined after the first month post stroke [4,5]. In addition, the projects will investigate the predictive value of TMS [58-62] and the clinical significance of changing fMRI activity [55,56] in relation to functional recovery of the paretic upper limb [4,10] (Relevance of project B1 of EXPLICIT). In addition, it is not known how patients learn to deal with their reduced ability to modulate and coordinate the upper limb after stroke and what role compensation strategies play in this. (Relevance of project B2 of EXPLICIT). Finally, it is unknown how changes in stiffness and spinal reflex properties interfere with upper limb recovery (Relevance of project B3 of EXPLICIT). A better understanding of the neurobiological drivers of functional recovery will allow clinicians to define both the optimal treatment strategy and its time window in rehabilitation services after stroke in the near future. In fact, the knowledge produced by the projects in the EXPLICIT-stroke programme will further underpin the concepts of motor recovery and motor learning in stroke rehabilitation by addressing the key question: what exactly do patients learn when functional improvement is observed after stroke? Therefore, EXPLICIT may serve as a template for understanding functional recovery by elucidating the longitudinal relationship between the body functions, body structures, activities and participation of International Classification of Functioning (ICF, relevance project C of EXPLICIT).

Answers to different A, B and C project are expected at the end of 2012.

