**Methods/design:**

180 participants suffering from an acute, first-ever ischemic stroke will be recruited. Functional prognosis at the end of the first week post stroke is used to stratify patient into a poor prognosis group for upper limb recovery (N = 120, A2 project) and a group with a favourable prognosis (N = 60, A1 project). Both groups will be randomized to an experimental arm receiving respectively modified CIMT (favourable prognosis) or EMG-NMS (poor prognosis) for 3 weeks or to a control arm receiving usual care. Primary outcome variable will be the Action Research Arm Test (ARAT), assessed at 1,2,3,4,5, 8, 12 and 26 weeks post stroke. To study the impact of modified CIMT or EMG-NMS on stroke recovery mechanisms i.e. neuroplasticity, compensatory movements and upper limb neuromechanics, 60 patients randomly selected from projects A1 and A2 will undergo TMS, kinematical and haptic robotic measurements within a repeated measurement design. Additionally, 30 patients from the A1 project will undergo fMRI at baseline, 5 and 26 weeks post stroke.

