(1) Is an early modified CIMT programme more effective in terms of recovery of the paretic upper limb than conventional care in stroke patients with a favourable prognosis for recovery of the upper limb? (Project A1)

(2) Is an early EMG-NMS programme for wrist and finger extensors more effective in terms of return of dexterity than conventional care in patients with initially poor prognosis for upper limb recovery? (Project A2)

(3) Are modified CIMT-induced gains reinforced by recruitment of cortical activation in the ipsilesional hemisphere when compared to usual care? (Project B1)

(4) Can improved performance of a functional reaching task be explained on the basis of behavioural compensation strategies? (Project B2)

(5) How and to what extent do wrist neuromechanical properties, i.e. stiffness, motor function and control change in the first 6 months post stroke? (Project B3)

(6) Does early intervention affect endpoint neuromechanics (Project B3)

(7) How are improvements in dexterity longitudinally related to changes observed in kinematics, neuromechanics and cortical activation (Project C).

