### The A projects of Explicit

The 'A' projects comprise two RCTs investigating the effectiveness of early interventions on paretic upper limb recovery in a 3-week programme starting in the second week post stroke and ending in the fourth week. In the first RCT (project A1), 60 first-ever MCA stroke patients with a National Institute of Health Stroke Score, NIHSS 1 or 2 and a voluntary extension of wrist and fingers of at least 10 degrees assessed at the end of the first week post stroke will be randomized to either an experimental group undergoing task-oriented exercises i.e. shaping procedures of the upper limb, supplemented by modified constraint-induced movement therapy (modified CIMT), or a control group. All patients will be recruited in four medical centres participating in EXPLICIT, i.e. Leiden University Medical Centre, LUMC; VU University Medical Centre, VUmc; Radboud University Medical Centre, RUMC and University Medical Centre Utrecht, UMCU.

In the second RCT (project A2), 120 patients with an initially poor prognosis for recovery of dexterity at the end of the first week, i.e. NIHSS score 3 or 4 and no voluntary control of the paretic upper limb, will be recruited and randomized either to an intervention group receiving conventional care supplemented by EMG-triggered electrotherapy (EMG-NMS) to stimulate wrist and finger extensors or to a control group.

After the intake procedure, which will include the first assessment of outcome variables, we will apply separate restricted randomization procedures (in permuted blocks) with random number tables for each participating university medical centre and for each of the projects A1 and A2. Concealed allocation will be effectuated with sealed opaque envelopes. Before randomization, patients and their families will be informed that all interventions may improve outcome, but that they will remain naive with respect to the supposed efficacy of the experimental condition to which they have been allocated. Nurses, speech therapists and social workers will continue to provide regular care depending on the patients' needs.

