#### Design and intervention

In the modified CIMT trial, patients in the experimental group will receive 30 minutes of task-oriented training of the upper extremity, aimed at improving dexterity of the paretic arm (i.e. shaping) for 5 days a week over 3 consecutive weeks. Task difficulty will be progressively increased using behavioural techniques of shaping and successive approximation [34]. In addition, the Padded Safety Mitt (Sammons Preston # 6727; Sammons Preston, Inc, Bolingbrook, IL, USA) will be applied for 2 hours to immobilize the non-paretic arm following each treatment session (excluding weekends). During toileting and under other circumstances that require safe balance, patients will be allowed to remove the padded safety mitt. The content and duration of the modified CIMT therapy as well as the shaping exercises will be recorded in a patients' log reflecting different treatment goals. Conventional care will consist of exercise therapy based on the principles of the NDT concept for a restricted one-by-one intervention time of 30 minutes per working day, 5 days a week for 3 consecutive weeks excluding weekends. Content and daily duration of conventional therapy will be recorded in the patient logs using different treatment codes for exercise intervention types and intervention goals (See for example Kwakkel et al [8]). The modified CIMT programme is focused on regaining voluntary wrist and finger extension of the paretic hand by intensive exercise therapy 2 times a day 30 minutes for 3 weeks. The protocol for modified CIMT is available at .

All therapy sessions will be individually applied by a local trained physical therapist (PT) and/or occupational therapist (OT) working in one of the participating university medical centres, or, if a patient is discharged earlier, in a regional rehabilitation centre.

After 3 weeks, the intensity of the interventions implemented by the OTs and PTs will be standardized in both arms of project A1 and restricted to exercise therapy alone, given for a maximum of 30 minutes per working day. Duration and aims of interventions implemented by PTs or OTs will be monitored by means of monthly phone calls by the local member of the project staff at the university medical centre.

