#### Design and intervention of project A2

In the second week post stroke, patients with an initially poor functional prognosis who have been allocated to the control group will engage in passive range-of-motion exercise and facilitation of voluntary movements for 30 minutes per week day, whereas the experimental group will receive EMG-triggered NMS (Stiwell Med 4, Otto Bock Healthcare Products GmbH, Vienna, Austria) of wrist and finger extensors each day for 3 periods of 30 minutes per working day during 3 consecutive weeks. The cyclic stimulation will be biphasic, with a pulse width of 200 μsec and intensity up to 29 mA with a frequency of 50 Hz. Patients are asked to imagine the dorsiflexing movement of fingers and wrist on the paretic side. This causes some initial muscle activity which, when detected by the EMG electrodes, amplified and presented once again to the muscle, may elicit a genuine contraction of the wrist extensors [40]. For those patients showing no EMG activity, the extensors of the non-paretic hand will be used as a trigger to activate the paretic hand. This new mode of electrical stimulation has been claimed to be superior to other types of electrical stimulation programme [18,40]. Finally, patients may learn to facilitate extensor activitity of wrist and fingers by simultaneously abducting their paretic arm (often described as Soques phenomenon). Details of the EMG-NMS treatment protocol is available at .

The intensity and content of the EMG-NMS as well as other therapies applied will be recorded in a patient log-book. Both groups will receive usual care in terms of lower limb training. After 3 weeks, usual care will be restricted to a maximum of 30 minutes of upper limb practice, monitored by monthly phone calls by the project staff. All therapy sessions will be individually applied by local physical (PT) and/or occupational (OT) therapists working at the local setting (UMC and local rehabilitation centre) where patients have been admitted. For this latter purpose, PTs and OTs who participate in EXPLICIT will have a training course in the preparation phase.

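### Project A2 is hypothesised against an equally intensive control programme, but the design gives 90 minutes of EMG-NMS a day against 30 minutes of control exercise

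*Protocol article*

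**What the plan says.** **A2, the hypothesis.** The Discussion names two hypotheses for the programme. The second is that an early EMG-NMS programme for wrist and hand extensors "may increase the likelihood of return of dexterity compared to an equally intensive conventional training programme".

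**A2, the treatments.** Under Design and intervention of project A2, the experimental arm receives EMG-triggered stimulation "of wrist and finger extensors each day for 3 periods of 30 minutes per working day during 3 consecutive weeks". Control patients "will engage in passive range-of-motion exercise and facilitation of voluntary movements for 30 minutes per week day". The same section mentions lower-limb training as usual care for both groups and says that other therapies are logged. It then adds: "After 3 weeks, usual care will be restricted to a maximum of 30 minutes of upper limb practice".

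**A2, the other statements of the comparison.** The Abstract (Methods/design) has patients randomised to "EMG-NMS (poor prognosis) for 3 weeks or to a control arm receiving usual care". Research question 2, at the end of the Background, asks whether EMG-NMS is "more effective in terms of return of dexterity than conventional care in patients with initially poor prognosis for upper limb recovery". The section on the A projects describes "an intervention group receiving conventional care supplemented by EMG-triggered electrotherapy (EMG-NMS) to stimulate wrist and finger extensors", compared with a control group. None of these sets a condition of equal dose.

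**A1.** Under Design and intervention for project A1, the experimental arm's task-oriented training is first given as 30 minutes, five days a week for three weeks. Later in the same paragraph the modified CIMT programme is described as two 30-minute exercise sessions a day for three weeks. The control arm gets 30 minutes per working day.

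**The concern.** A hypothesis of benefit over an equally intensive comparator claims that treatment time is held constant, so that any difference reflects the kind of treatment. The A2 design does not hold it constant. This matters here because the article itself presents treatment intensity as a factor thought to drive recovery (Abstract, Background, A1 hypotheses). If EMG-NMS does better, the extra treatment time is a rival explanation that the trial cannot exclude. A reader who relies on the Discussion would credit A2 with a dose-matched control that it does not have.

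In A1 the worry is smaller. The two descriptions of the experimental training leave it unclear whether therapist time is matched between the arms.

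**Working it through.** The plan gives no dose ratio of its own to reproduce, beyond the 1:1 implied by the Discussion.

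**A2, per working day (named upper-limb sessions)**
- Experimental, from the A2 design section: 3 × 30 = 90 minutes.
- Control, from the same section: 30 minutes.
- Ratio: 90 / 30 = 3. Difference: 90 − 30 = 60 minutes a day.

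**A2, if the conventional session is kept.** The section on the A projects describes EMG-NMS as a supplement to conventional care. If this means that the experimental arm also has the control arm's 30-minute session:
- Experimental: 90 + 30 = 120 minutes. Ratio: 120 / 30 = 4.

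The A2 design section itself states 90 minutes. The idea that 90 is a minimum comes only from the A projects section.

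**A2, over the intervention period.** Three weeks of five working days is 15 days.
- EMG-NMS: 90 × 15 = 1350 minutes (or 120 × 15 = 1800).
- Control: 30 × 15 = 450 minutes, *assuming* that the control session runs for all three weeks. The A2 design section introduces it with reference to the second week post stroke and attaches the three-week duration only to EMG-NMS.
- Difference on that assumption: (1350 − 450) / 60 = 15 hours.

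The daily ratio does not depend on this assumption.

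**Does anything else in the article restore equality?**
- The 30-minute limit on upper-limb practice begins after three weeks, when the intervention is over.
- The only care said to be common to both arms is lower-limb training.
- Other therapies are recorded but not fixed, so total treatment time per arm cannot be derived. No sentence gives the control arm matching time.
- The A1 section uses the word for treatment time: after three weeks "the intensity of the interventions implemented by the OTs and PTs will be standardized in both arms of project A1", with a maximum of 30 minutes per working day. On that usage, 90 against 30 is not equal intensity.

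**A1, over 15 working days**

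| Reading of the experimental training | Experimental (min) | Control (min) | Ratio |
|---|---|---|---|
| 30 minutes a day | 30 × 15 = 450 | 30 × 15 = 450 | 1:1 |
| 2 × 30 minutes a day | 60 × 15 = 900 | 30 × 15 = 450 | 2:1 |

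The gap between the two readings is (900 − 450) / 60 = 7.5 hours per patient.

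**The case against.** **The A2 point rests on one phrase in a Discussion.** The research question, the A projects section, the A2 hypotheses and the A2 power analysis carry no equal-dose condition. Conventional care plus an add-on, against conventional care, is a legitimate contrast, and the unequal session times are openly stated. This stands, and it limits the point. A reader might infer that A2 is invalid or cannot answer its question. The documents do not support that: research question 2 is answerable as posed. What fails is the Discussion's version of the hypothesis.

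**Intensity might mean something other than minutes.** In the A2 sections the word also refers to stimulation current and stimulus strength, and the A1 usage concerns care after the intervention. The A1 sentence is therefore weaker support than it first appears. Still, the article shows no sense of the word in which the two A2 arms would be equal.

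**The larger totals are not all in the text.** This is correct. It is tempting to state 15 extra hours, or a 3:1 ratio of total treatment, as fact. The first assumes three weeks of control sessions, and the second ignores logged therapies of unknown amount.

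**A1 may be loose drafting.** A reader might infer a flat contradiction in dose. The first A1 sentence does not say once a day, so the later one may simply supply the frequency. Alternatively, one shaping session plus one conventional session would give two a day, although the article does not say so and assigns both to the modified CIMT programme. The article also points to a separate treatment protocol. These readings make A1 an unresolved ambiguity and not a demonstrated error.

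**Conclusion.** The A2 point holds. The Discussion attributes to the comparison a property, equal intensity, that the design lacks. The named upper-limb sessions differ by 3:1 per working day, or 4:1 if the conventional session is retained in the experimental arm. The figure of 1350 against 450 minutes is conditional on a three-week control programme. A positive result would support the EMG-NMS package, including its extra treatment time, over conventional care. It would not support EMG-NMS at equal intensity.

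The A1 point holds with lower confidence, and only as an ambiguity: from the article alone, therapist time in the two arms could be 1:1 or 2:1. The A1 hypotheses remain answerable at either dose.

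**What to change.** - **A2:** delete the equal-intensity wording from the second programme hypothesis in the Discussion, so that it agrees with the Abstract, research question 2 and the A projects section. Word the A2 conclusion as the EMG-NMS package against conventional care.
- **A1:** correct the design paragraph to the single daily training dose given in the treatment protocol.

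Both are changes of wording. Randomisation, sample size, endpoints and data collection are untouched. The one real cost is that the A2 claim becomes narrower than the Discussion now implies.
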